# Effectiveness and safety of nintedanib in prevention of pulmonary fibrosis induced by bleomycin in malignant ovarian germ cell tumour: study protocol for a randomised, double-blind, placebo-controlled trial

**DOI:** 10.1136/bmjopen-2023-074963

**Published:** 2023-12-09

**Keywords:** Clinical Trial, Gynaecological oncology, Protocols & guidelines, ONCOLOGY

## Abstract

**Introduction:**

Bleomycin is a crucial and irreplaceable chemotherapy regimen for malignant ovarian germ cell tumours (MOGCTs) but its toxicities especially pulmonary fibrosis have limited the dose of treatment efficacy and decreased the patients’ quality of life (QoL). Nintedanib has been approved for treating progressive fibrosing interstitial lung diseases and has shown potential anti-tumour effects. This study aims to evaluate the effectiveness and safety of nintedanib in the prevention of pulmonary fibrosis induced by bleomycin in MOGCTs patients.

**Methods and analysis:**

This is a multicentre, randomised, double-blinded, placebo-controlled clinical trial. We will enrol a total of 128 patients who will be randomly assigned to the nintedanib group and placebo group in a 1:1 ratio. Standard bleomycin, etoposide and cisplatin chemotherapy will be given to each MOGCT patient. In addition, patients assigned to nintedanib and the control group will be given oral nintedanib 150 mg two times per day and placebo one tablet two times per day until 1 month after the last cycle of bleomycin therapy, respectively. The primary outcome is the decline of forced vital capacity (FVC). The secondary outcomes are the decline of other pulmonary function indices (forced expiratory volume in 1 s; FVC pred%, carbon monoxide diffusion capacity) and the patients’ QoL, oncological and fertility outcomes. We will use electronic case report forms to record all the participants’ data and SPSS V.27.0/STATA V.16.0/Graphpad Prism V.8.0 to conduct statistical analysis.

**Ethics and dissemination:**

The Ethics Committee of Peking Union Medical College Hospital has approved the study (I-23PJ400). Written informed consent will be obtained from all participants/guardians. Study results will be submitted to peer-reviewed medical journals for publication and presented at academic conferences.

**Trial registration number:**

ChiCTR2300070492.

STRENGTHS AND LIMITATIONS OF THIS STUDYThis trial aims to evaluate the effectiveness and the safety of nintedanib in malignant ovarian germ cell tumours patients receiving bleomycin chemotherapy.This prospective, randomised, double-blinded, placebo-controlled design increases the reliability of the results and conclusions.The non-invasive test of pulmonary function and other outcomes will enhance the feasibility and compliance of participants.The limitation is that it may need more time to enrol enough participants due to the rarity and need a long-term follow-up to assess some secondary outcomes and the single-centre nature.

## Introduction

Malignant ovarian germ cell tumours (MOGCTs) are heterogeneous non-epithelial ovarian malignant tumours that originate from the abnormal differentiation and malignant transformation of primordial germ cells of embryonic gonads. MOGCTs are rare and only account for about 3% of all ovarian malignancies, with an estimated incidence of 0.4/100 000 women years and mostly affected patients about 20 years.^1 2^ It is estimated that approximately 60%–70% of MOGCTs patients are diagnosed with International Federation of Gynecology and Obstetrics (FIGO) stage I, and only less than 5% are with FIGO stage IV diseases on initial treatment, therefore, the prognosis of MOGCTs patients is usually satisfactory.^1 3^

Currently, the standard treatment for MOGCTs patients can be a combination of surgery and adjuvant chemotherapy (bleomycin, etoposide and cisplatin, BEP regimen) based on tumour stage and/or grade, while fertility-sparing surgery is always recommended in childbearing or young patients.^4 5^ Bleomycin is the crucial and irreplaceable regimen for chemotherapy in MOGCTs.^6^ However, the toxicities associated with bleomycin including acute and later-onset pulmonary toxicity have limited the dose of the regimen, in terms of treatment efficacy and have decreased the quality of life (QoL) in these young patients.^7^ The risk of pulmonary fibrosis is an important adverse effect (AEs) of bleomycin, and it has been reported that pulmonary toxicity induced by bleomycin occurred in 6.8%–46% of patients, with bleomycin-related mortality of about 3%–5%.^8^ Other AEs are less common, such as fever, hypersensitivity and organising pneumonitis.^9^

Tumour relapse usually occurs within 2 years after treatment in MOGCTs patients.^10^ Although chemotherapy after relapse can achieve a complete remission rate of about 75%, about one-third of advanced MOGCTs patients may experience recurrence or chemotherapy resistance in a short period, resulting in poor survival outcomes.^7 11^ Relapsed MOGCTs are usually not curable partly due to intolerance to bleomycin or not having enough therapeutic doses of bleomycin, whereas other chemotherapy regimens are not effective.^12^

Hence, it has always been emphasised to alleviate bleomycin-induced toxicities, especially pulmonary fibrosis. Although the exact mechanisms of pulmonary fibrosis caused by bleomycin remain uncertain, it has been proposed that inflammatory reaction and subsequent fibroplasia may play an important role in the pathophysiology of pulmonary fibrosis.^13 14^ Nintedanib is a small-molecule tyrosine kinase inhibitor that targets platelet-derived growth factor receptor-α and β, fibroblast growth factor receptor-1–3 and vascular endothelial growth factor receptor-1–3.^15^ Nintedanib has been approved for the treatment of idiopathic pulmonary fibrosis (IPF) in many countries, and several clinical trials have proven its effectiveness and safety in the treatment of IPF.^16 17^ Recently, Gundogan *et al* also reported a 13-year-old lymphoma patient treated with a bleomycin-containing chemotherapy regimen who developed bleomycin-induced pneumonia that was successfully treated with nintedanib.^18^ Moreover, nintedanib also showed antitumour effects in some reports.^19 20^

However, none of these studies provide evidence of nintedanib in the treatment of pulmonary fibrosis in MOGCTs. Therefore, a prospective, double-blinded, randomised control trial is designed to evaluate the effectiveness and safety of nintedanib in MOGCTs patients receiving bleomycin.

### Objective

The primary aim of this randomised, control trial is to determine whether nintedanib can alleviate the reduction decline of forced vital capacity (FVC) in MOGCTs patients who receive BEP chemotherapy. The secondary objective is to evaluate the decline of other pulmonary function indices (forced expiratory volume in 1 s, FEV1; FVC pred%, carbon monoxide diffusion capacity, DLCO), the safety of nintedanib treatment, oncological and fertility outcomes, and QoL in MOGCTs patients.

## Methods and analysis

### Study design

This is a prospective, randomised, double-blinded, placebo-controlled clinical trial that was registered at the Chinese Clinical Trial Registry on 14 April 2023 (ChiCTR2300070492). It has been approved by the Ethics Committee of Peking Union Medical College Hospital and will be conducted in accordance with the Declaration of Helsinki and strictly follow the latest Consolidated Standards of Reporting Trials recommendations,^21^ Standard Protocol Items: Recommendations for Interventional Trials statement^22^ (online supplemental table 1). For all patients who will participate in this study, written informed consent will be obtained before treatment.

10.1136/bmjopen-2023-074963.supp2Supplementary data

A total of 128 participants diagnosed with MOGCTs treated with BEP chemotherapy will be enrolled in the trial. The total screening and enrolling period will last for about 2.5 years in estimation, and they will be followed up for at least 1 year (up to 5 years) after treatment. The enrolment is planned to start on 1 October 2023 and end on 1 April 2026. The participants will be randomised and assigned to either the intervention group or the placebo group in a 1:1 ratio using a central randomisation system. In addition to standard adjuvant chemotherapy, they will be given nintedanib (150 mg) or placebo in granule form twice a day before chemotherapy till 1 month after the last cycle of chemotherapy.

### Participants

The inclusion criteria are listed as follows:

Newly diagnosed MOGCTs patients who will be treated with BEP chemotherapy or bleomycin-based chemotherapy.Age between 14 and 40 years.Pulmonary function test can be completed.FVC≥45% of normal predicted value and DLCO≥60% of normal predicted value.Patients who agree and sign the written informed consent, and with good compliance.

Patients who meet the following criteria will be excluded:

Patients with pre-existing interstitial lung disease.Patients with severe medical diseases, severely impaired liver function (transaminase increased to 2.5 times the upper limit of normal) and severely impaired renal function (creatinine clearance rate <30 mL/min).Combined with other reproductive system malignant tumours.Complicated with deep vein thrombosis, pulmonary embolism, myocardial infarction, cerebral infarction and other diseases.Combined with other diseases requiring long-term hormone therapy.Patients with chronic obstructive pulmonary disease or pulmonary hypertension that influence pulmonary function.Patients who are considered not suitable to be enrolled by researchers.

### Recruitment of patients and data collection

#### Participants inclusion

The recruit proclamation that includes a summarised description of the study will be released through webpages, in inpatient and outpatient areas. All the patients with MOGCTs (or their guardians in the case of juveniles) who visited our hospital will be evaluated whether they are suitable for entry into the clinical trial. The final pathology confirmation will be determined by two experienced pathologists at Peking Union Medical College Hospital. Then, for those potentially eligible MOGCTs patients, the study team will ask them or their guardians whether they are willing to participate in the study. Once written informed consent is obtained, members of the research team will collect the basic demographic information. Otherwise, the reasons why patients are excluded will also be recorded.

#### Study group assignment

After the exclusion and inclusion process, we will perform the concealed study group assignment based on the central randomisation system. An independent statistician will generate a randomisation sequence for all the eligible MOGCTs patients. The patients will be randomly allocated to either nintedanib (experimental) or placebo (control) groups. For all the MOGCT patients enrolled in this trial, a standard treatment, namely comprehensive fertility-sparing surgical staging, or radical surgical staging plus BEP chemotherapy for 3–4 cycles, in accordance with the ESMO guidelines,^5^ no matter whether they are assigned to which group. In addition to standard treatment, patients allocated to the nintedanib group will be given oral nintedanib 150 mg two times per day before the first cycle of BEP chemotherapy until 1 month after the last cycle of BEP chemotherapy. Accordingly, patients in the control group will be given an oral placebo one tablet per time, two times per day before the first cycle of BEP chemotherapy until 1 month after the last cycle of BEP chemotherapy. The nintedanib and placebo will be provided by the study team and the appearance will be the same, without identifiable labels or packaging. The patients will be requested to record the medication and return the packaging to researchers after treatment. The flow chart (figure 1) shows the simplified procedure of group allocation, interventions and outcomes assessment.

**Figure 1 F1:**
[figure not shown]
The flow chart demonstrates the simplified process of group allocation, interventions and outcomes assessment. BEP, bleomycin, etoposide and cisplatin; DLCO, carbon monoxide diffusion capacity; EFV1, forced expiratory volume in 1 s; FVC, forced vital capacity; MOGCT, malignant ovarian germ cell tumours; QoL, quality of life.

#### Termination of therapy (nintedanib or placebo)

The planned end of treatment (till 1 month after the last cycle of BEP chemotherapy).Termination of treatment due to severe AEs.Withdrawal of written informed consent.

#### Management in case of patients who could not complete pulmonary function test

In patients who may not be able to receive pulmonary function tests due to bleomycin-induced acute lung injury, arterial blood gases and high-resolution pulmonary CT will be performed to indirectly examine the pulmonary function. Meanwhile, it is also an adverse event that will be recorded in this trial. Pulmonary function tests will be performed after recovery or until those patients can complete this examination. For patients whose general condition has deteriorated due to MOGCT progression, if such patients had been enrolled in this trial, they would have recorded baseline and dynamic pulmonary function tests until they could not finish the pulmonary test. If they have not already finished the complete treatment for MOGCT and cannot continuously receive bleomycin-based chemotherapy, these adverse events will be recorded as positive events during the trial to evaluate the safety of nintedanib.

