### Outcomes

#### Primary outcomes

The primary outcome of the study is the declined degree of FVC in MOGCT patients who receive BEP chemotherapy revealed by respiratory function test. The secondary outcomes are the decline of other pulmonary function indices (FEV1; FVC pred% and DLCO), the safety of nintedanib treatment, oncological and fertility outcomes, and QoL in MOGCTs patients.

The safety assessment of nintedanib is measured by patients’ vital signs, auxiliary examinations and AEs. The auxiliary examinations include blood tests (routine analysis, liver and kidney function, etc), urine and stool examinations. We will record any AE during the treatment and follow-up period. The definition and classification of AEs based on the CTCAE5.0. Treatment will be continued in case of grade 1 or tolerable grade 2 AEs, and temporary termination of treatment will be applied in case of the first occurrence of intolerable grade 2 or grade 3 AEs until recovery to grade 0–1 or grade 2 AEs. However, permanent termination of nintedanib medication will be considered on the second time of intolerable grade 2 or grade 3 AEs, no matter the previous toxicities or newly identified toxicities.

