### Data management and statistical analysis

We will use an electronic case report form to collect data, and an electronic database will be subsequently generated. All the investigators need to be authorised to access the data and will be required to maintain data confidentiality. A periodic indication to update outcomes’ information during the follow-up will also be set up. After completion of the study, data will be stored for at least 20 years at a central data drive at the Peking Union Medical College Hospital. The datasets used and/or analysed during the current study can be obtained from the principal investigator on reasonable request. Moreover, a written, signed data-sharing agreement will be required to get data access.

The variables will be described according to the distributions, namely, mean±SD (range) for normally distributed continuous variables, otherwise they are described as medians and IQRs. Counts (percentages) will be used to present discrete variables. Methods for comparisons of variables between two groups will also be determined according to the data types. For oncology outcomes, including recurrence-free survival, overall survival and disease-specific survival, we will use the Kaplan-Meier method (log-rank test). The univariate analysis will be performed to screen factors that should be subjected to multivariate analysis, and we set the cut-off p values as 0.10 in univariate analysis. The Cox regression model or logistic regression model will be conducted in multivariate analysis. SPSS (V.20.0; SPSS), GraphPad Prism (V.8.0; GraphPad Software, La Jolla, California, USA) or STATA (SE V.12, StataCorp) software will be applied to perform the statistical analysis when appropriate. We set the statistical significance cut-off as 0.05 (two-tailed p value).

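### Stopping bleomycin because of tumour progression is recorded as an event in the nintedanib safety evaluation, which mixes a tumour outcome with drug toxicity

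*Protocol article*

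**What the plan says.** The section of the protocol article on patients who could not complete the pulmonary function test deals with two groups in turn.

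- **Bleomycin lung injury.** Patients who cannot be tested for this reason have substitute examinations, and the injury has its own recording rule: "Meanwhile, it is also an adverse event that will be recorded in this trial".
- **Tumour progression.** The text then turns to a second group: "For patients whose general condition has deteriorated due to MOGCT progression". Their pulmonary function is recorded for as long as they can be tested. The next sentence sets a condition, "If they have not already finished the complete treatment for MOGCT and cannot continuously receive bleomycin-based chemotherapy", and a consequence: "these adverse events will be recorded as positive events during the trial to evaluate the safety of nintedanib".

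Elsewhere the two kinds of outcome are kept apart. The secondary outcomes include "the safety of nintedanib treatment, oncological and fertility outcomes, and QoL in MOGCTs patients". For adverse events the article states: "The definition and classification of AEs based on the CTCAE5.0". Cancer outcomes have their own analysis, by Kaplan-Meier and log-rank: "For oncology outcomes, including recurrence-free survival, overall survival and disease-specific survival".

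**The concern.** The article names the tumour as the cause of deterioration in the second group, yet the consequence is an entry in the evaluation of the study drug. The section does not ask for the reason for stopping bleomycin to be kept with the event.

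It matters because safety is a stated objective and the Harms section says that safety data for nintedanib with bleomycin-based chemotherapy in these patients are limited. With about 64 patients per arm, a few misclassified entries can change how a small safety table reads.

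The arms may also differ in progression for a reason unrelated to toxicity. The Introduction says that "nintedanib also showed antitumour effects in some reports", and the Abstract and Discussion make similar remarks. Fewer progressions on nintedanib would lower its count of these events and so offset some real toxicity.

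**Working it through.** The plan gives no figure to reproduce, because the point concerns an event definition. The check is one of reading, followed by an illustration.

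**Reading.** In the sentence with the condition, the pronoun refers to the patients named just before it, those with tumour progression. Lung injury has already been dealt with. The phrase for the adverse events has no clear antecedent, so the wording is loose. On a broader reading (any inability to continue bleomycin) the sentence would still pool progression with lung toxicity. The sample size section allows for up to 10% of patients being unable to continue bleomycin because of pulmonary fibrosis, which is the harm nintedanib is meant to prevent. The reasons need separating on either reading.

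**Inputs from the document.** 128 patients allocated 1:1, so 64 per arm. One event is 1/64 = 1.6 percentage points of an arm.

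**Assumed inputs.** The document gives no toxicity or progression rates by arm, so all rates below are assumptions. They also assume that the safety summary is the proportion of patients with any event, a summary the article does not define.

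*Equal progression, events in different patients.* Toxicity is 10% v 3%, with progression c added to both arms. The ratio is (0.10 + c)/(0.03 + c).

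| c | Rates | Ratio | Difference |
|---|---|---|---|
| 0 | 10% v 3% | 3.3 | 7 points |
| 2% | 12% v 5% | 2.4 | 7 points |
| 5% | 15% v 8% | 1.9 | 7 points |
| 10% | 20% v 13% | 1.5 | 7 points |

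The ratio falls and the difference does not move.

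*Toxicity and progression independent.* The combined rate in each arm is 1 − (1 − toxicity)(1 − progression). Rates are nintedanib v placebo.

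| Toxicity | Progression | Combined | Difference | Ratio |
|---|---|---|---|---|
| 20% v 10% | none counted | 20.0% v 10.0% | 10.0 points | 2.00 |
| 20% v 10% | 5% v 5% | 24.0% v 14.5% | 9.5 points | 1.66 |
| 20% v 10% | 10% v 10% | 28.0% v 19.0% | 9.0 points | 1.47 |
| 20% v 10% | 5% v 10% | 24.0% v 19.0% | 5.0 points | 1.26 |
| 20% v 10% | 5% v 15% | 24.0% v 23.5% | 0.5 points | 1.02 |
| 10% v 10% | 5% v 5% | 14.5% v 14.5% | 0 points | 1.00 |
| 10% v 10% | 5% v 10% | 14.5% v 19.0% | −4.5 points | 0.76 |

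Equal progression creates no false difference when toxicity is equal, and shrinks a true difference only slightly (10.0 to 9.5 or 9.0 points). Fewer progressions on nintedanib can hide excess toxicity, or make the drug look safer than placebo when toxicity is equal.

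**How common the event may be.** The Introduction puts 60–70% of patients at stage I and fewer than 5% at stage IV, and places relapse usually within 2 years after treatment. The rule applies only to patients who deteriorate before completing 3–4 cycles. At an assumed 2%, that is 0.02 × 64 = 1.3 patients per arm.

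**The case against.** The strongest objection is that the sentence governs recording. The article measures safety by vital signs, auxiliary examinations and adverse events. It defines no pooled safety proportion and names no test or ratio for one. If events are tabulated by type and grade, a progression entry does not alter the comparison of diarrhoea or liver enzymes. How adverse events are tabulated may well be settled in the full protocol or the SAP, which are not shown. This stands, and it limits the point to safety summaries that include these events. It does not remove the point, because the sentence states that the events serve the evaluation of nintedanib's safety.

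It is also fair to say that the assumed rates have no basis in the document, and that the cases where a toxicity difference nearly vanishes need a marked imbalance in progression. The tables show direction and mechanism; they do not estimate this trial's bias.

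Three stronger readings are tempting and are not supported:

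- A reader might infer that the safety comparison no longer measures drug harm. CTCAE-defined events are still collected, and these entries are probably few.
- A reader might infer bias in either direction, so that progression could also imitate toxicity. The article cites only antitumour effects. Nothing in it suggests more progression on nintedanib.
- A reader might infer that counting an event under both safety and oncology is itself an error. It is not. On-treatment progression is also not named among the survival outcomes, although that list is open.

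Finally, simply deleting these events from the safety record would go too far. The article undertakes to record any adverse event, and exclusion could hide harm if nintedanib impaired completion of chemotherapy.

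**Conclusion.** The point holds in a limited form. On its plain reading, the article's rule places progression-related inability to continue bleomycin in the nintedanib safety evaluation, and so mixes a tumour outcome with drug toxicity. This is a stated rule, not a detail left to another document.

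Any bias between the arms requires progression to differ by arm. The only direction with support in the text is fewer progressions on nintedanib, which could partly mask excess toxicity. With equal progression the effect is dilution, mainly of a ratio. The size cannot be determined from the document and is probably small, at 1.6 points of an arm per patient. The primary FVC outcome is not touched by this rule. The conclusion rests on reading the pronoun as the progression group and on a safety summary that includes these events. The change is worth making because it is cheap and safety data in this population are limited.

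**What to change.** Reword the sentence along these lines: where a participant stops bleomycin early because the tumour has progressed, this is recorded as an oncological event in its own category, with progression as the reason for stopping, and not as a toxicity event of study treatment; any CTCAE event in that participant is recorded as usual.

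Then:

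- base the main safety comparison on CTCAE 5.0 events;
- tabulate early discontinuation of bleomycin by arm and by reason (lung toxicity, other toxicity, progression);
- show the safety summary with and without the progression-related events, so that no signal is lost if study treatment affects completion of chemotherapy.

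The cost is one sentence in the protocol, a reason-for-stopping field in the electronic case report form, and a judgement of the reason made blind to allocation. It adds no visits or tests and changes no treatment rule.
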